**Participants**			
Patient information and informed consent	X		
Demographics	X		
EQ-5D-5L	X	X	X
ReQOL	X	X	X
Patient activation measure	X	X	X
Multimorbidity Treatment Burden Questionnaire	X	X	X
De Jong Gierveld Loneliness Scale	X	X	X
Participant goals	X	X	X
Health Questionnaire including number of health screenings and service use in last 6 months	X	X	X
Acceptability 1. Acceptability of intervention measure 2. Interview		X	
Appropriateness 1. Intervention appropriateness measure 2. Interview		X	
Feasibility 1. Feasibility of intervention measure 2. Interview		X	
Fidelity-interview		X	
Barriers and facilitators-interview		X	
Adoption-interview		X	X
Sustainability- Interview		X	X
Unintended consequences-interview		X	X
Experience of the intervention-interview		X	

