## Methods and analysis

### Design

This is a feasibility hybrid II effectiveness-implementation randomised controlled trial. Hybrid type II trials [18] are at the cutting edge of applied health research and are used to jointly assess the clinical effectiveness and implementation strategies of evidence-based interventions so that findings can be interpreted in the light of how best to implement such interventions at scale and with sustainability, including economic viability. The schedule of enrolment, interventions and assessments is shown in Table 2.

**Table 2 Tab2:** Data collection plan

	Baseline assessment	Follow-up assessment 1 (at end of intervention or after 9 months)	Follow-up assessment 2 (6 months after end of intervention or 9 month assessment)

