### Participant recruitment

We will recruit participants from CMHTs across all four South London boroughs that are covered by SLaM services—namely the boroughs of Lambeth, Lewisham, Southwark and Croydon. Participants will be recruited using two methods.
Directly recruited from the community teams by staff identifying and recruiting people who are eligible for the study. Staff will be made aware of the eligibility criteria of the study.Using the SLaM Consent for Contact (C4C) service to identify people using CMHTs who have already consented to be approached by researchers to take part in research projects.

Once potential participants have been identified, they will be contacted by a researcher who will explain the purpose and nature of the study to them. If they are interested in taking part, a researcher will meet with them and give them the patient information sheet to read and answer any questions. If possible these meetings will be face-to-face, if not they will be by telephone or on Microsoft Teams. If they are still interested in taking part, they will complete a written consent form. If the meeting is not face-to-face, consent forms can either be posted to the participant or they can complete an online consent form. A baseline assessment will then be done which will also be either face-to-face or remotely. After this assessment, they will be allocated to either the intervention or control group (see “Randomisation” section for details below).

Participants in the intervention group will then follow the intervention as outlined above. Participants in the control group will receive a copy of a workbook on managing physical health and a ‘Participant Physical Health Journal’. Both groups will be asked to complete follow-up assessments at 9 months and 15 months after baseline. All participants will be reimbursed £10 for each assessment, £30 in total.

If any participants lose mental capacity during the trial, they will be withdrawn from the study.

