#### Secondary outcomes

The following outcomes will be measured at baseline, and at the end of the intervention (9 months after baseline) and 6 after the end of the intervention.
Self-management using the 10-item Patient Activation Measure [22].Mental Health related Quality of Life using the 10-item Recovering Quality of Life (ReQoL) measure [23].Treatment burden using the 10-item Multimorbidity Treatment Burden Questionnaire [24].Loneliness using the 6-item De Jong Gierveld Loneliness Scale [25].We will record participant’s use of physical health services and physical health screenings.We will record demographic information including age, gender, ethnicity, educational level, living arrangements, employment status and relationship status.

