### Aim 3: Health economic evaluation of the intervention and implementation

#### An economic evaluation will be used to answer whether

The Health Champion approach warrants scaling-up given available evidence on implementation and intervention costs, evidence-based assumptions regarding the effectiveness of its implementation (e.g. anticipated levels of population ‘reach’) and likely impact of the intervention on quality of life and survival in the short- and longer-term.The extent of uncertainty in how cost-effective it would be to scale-up the Health Champion intervention for people with SMI, and the implications of decision uncertainty for commissioning choices.

The economic evaluation will be undertaken using decision analytic modelling approaches combined with a review and synthesis of current clinical, economic and epidemiological evidence (including that generated as part of the feasibility trial) of relevance to quantifying the consequences and cost-effectiveness of available decision options concerning scale-up. In support of this approach, the feasibility trial will be used as an opportunity to generate additional evidence and information necessary to support economic modelling.

The scores from the EQ-5D-5L will be used to calculate health-related quality of life changes and for estimating QALY outcomes. We will calculate the costs associated with the implementation of the intervention (time of volunteer coordinator and the Health Champions) and time taken to complete the intervention (by service users). We will also evaluate the cost of any changes in wider service user by participants.

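### A 6-month service-use recall at a 9-month follow-up leaves months 0–3 after allocation unrecorded in both arms

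*Protocol article*

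**What the plan says.** Table 2 (Data collection plan) has a single row, "Health Questionnaire including number of health screenings and service use in last 6 months", marked at baseline, follow-up 1 and follow-up 2. No different recall is given for any of the three.

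On timing, Participant recruitment states: "Both groups will be asked to complete follow-up assessments at 9 months and 15 months after baseline". The Secondary outcomes section agrees on follow-up 1, with outcomes "measured at baseline, and at the end of the intervention (9 months after baseline", and the Aim 1 Primary outcome section also equates the end of the intervention with month 9. The column headings of Table 2 are looser: "Follow-up assessment 1 (at end of intervention or after 9 months" and "Follow-up assessment 2 (6 months after end of intervention or 9 month assessment".

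On use of the data, Secondary outcomes says "We will record participant’s use of physical health services and physical health screenings", and Aim 3 says "We will also evaluate the cost of any changes in wider service user by participants" (the context shows that service use is meant). Aim 3 costs coordinator, Health Champion and service-user time separately.

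**The concern.** The 6-month recall fits the 6-month interval between the two follow-ups. It does not fit the 9-month interval between baseline and follow-up 1, so the first three months after allocation fall into no window.

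Two uses of the data are affected: the secondary outcome on service use and screenings, and the service-use inputs to the economic work. The missing period may also be unlike the rest. The Theory of Change (Table 1) expects Health Champions to help people attend physical health appointments and expects more screenings. The intervention section has goals set at the initial meeting. A one-off catch-up appointment or screening could therefore fall early.

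An analysis plan cannot recover data that were never collected. The Discussion says the study is meant to test the set of measures for a definitive trial, so the mismatch could be carried forward.

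**Working it through.** **Inputs**
- Recall length: 6 months at all three assessments (Table 2).
- Follow-up 1: t1 = 9 months after baseline (Participant recruitment; Aim 1 Primary outcome; Secondary outcomes).
- Follow-up 2: 6 months after follow-up 1 (Table 2 heading).
- Month 0: the baseline assessment. Allocation comes next: "After this assessment, they will be allocated to either the intervention or control group".

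**Reproducing the schedule.** Follow-up 2 = 9 + 6 = 15 months, which agrees with Participant recruitment.

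**Coverage.** Each window runs from (assessment time − 6) to the assessment time.

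| Assessment | Window (months) |
|---|---|
| Baseline | −6 to 0 |
| Follow-up 1 (month 9) | 3 to 9 |
| Follow-up 2 (month 15) | 9 to 15 |

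Months covered after allocation: 6 + 6 = 12 of 15. Gap: months 0 to 3, which is 3/9 = 33% of the time to follow-up 1 and 3/15 = 20% of the whole.

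**Sensitivity to the timing of follow-up 1.** Gap = max(0, t1 − 6). Months recalled from before baseline = max(0, 6 − t1).

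| t1 (months) | Gap (months) | Recalled months before baseline |
|---|---|---|
| 4 | 0 | 2 |
| 6 | 0 | 0 |
| 7 | 1 | 0 |
| 8 | 2 | 0 |
| 9 | 3 | 0 |
| 10 to 12 | 4 to 6 | 0 |

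Rows below 9 apply only if Table 2's end-of-intervention wording is followed for early finishers. The last row is an assumption: the Abstract starts the 9 months of support at the initial introduction, so follow-up 1 would be later than month 9 if it waited for the end of support after a delay in matching.

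**What scaling can and cannot repair.** Let a be the monthly rate of use in months 0–3 and b the rate in months 3–9.
- True use to month 9: 3a + 6b.
- Estimate scaled from the observed window: 6b × 9/6 = 9b.
- Error: 9b − (3a + 6b) = 3(b − a), which is zero only if a = b.

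For the difference between arms, write Δa and Δb for the differences in rates. The true difference is 3Δa + 6Δb and the scaled estimate is 9Δb. If the effect is confined to months 0–3 (Δb = 0), the estimate is 0 whatever the size of Δa.

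**After the change.** With recall since baseline at follow-up 1 and 6 months at follow-up 2, the windows are 0 to 9 and 9 to 15, and no month is uncovered.

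**The case against.** The strongest defence is that equal 6-month windows before, late in and after the intervention give like-for-like rates, identical in both arms, and that Aim 3 asks only for the cost of changes in use. That stands as far as it goes: service use remains a comparable outcome over a defined 6-month period. It does not bring months 0–3 into view.

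Several stronger readings are tempting, and the article does not support them:
- **That incremental cost per QALY will rest on 12 months of cost against 15 months of QALYs.** Aim 3 plans decision-analytic modelling combined with evidence synthesis, with the trial supplying inputs. It describes no summed 15-month cost divided by QALYs.
- **That totals are understated by 20%.** This follows only if raw counts are added (12/15 = 80%) and presented as 15-month totals, which the article does not say. With a constant rate of use, a monthly rate removes the shortfall.
- **That nothing is costed in months 0–3.** Delivery time is costed separately; the gap concerns wider service use.
- **That a third of the intervention itself is lost.** Matching and introduction follow allocation, so part of months 0–3 may precede any Health Champion contact.
- **That early catch-up use is established.** It is plausible from the Theory of Change but nowhere shown.

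It is also fair to say that the time qualifier in the table row may govern service use alone and not screenings. The questionnaire is not shown. The Control group section promises to record the physical health support that participants receive, but names no source, period or costing, so it does not clearly close the gap.

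**Conclusion.** The point holds for wider service use and, on the natural reading of the row, for health screenings. With follow-up 1 at month 9, the article's own figures leave 3 of the first 9 months and 3 of 15 overall uncaptured in both arms, and it names no other source that is to be costed. The consequence is the loss of any use, and of any between-arm difference, specific to months 0–3. How large that is cannot be judged from the article.

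The conclusion assumes that the questionnaire uses the recall stated in Table 2 and that follow-up 1 takes place at month 9. If early finishers were assessed early, as the Table 2 heading permits, the gap would shrink or the window would reach back before allocation. Controls have no Health Champion support to finish early, so the window could then differ between arms.

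Severity is moderate. The trial is a feasibility study with mainly descriptive aims, and EQ-5D-5L and acceptability, its primary outcomes, are untouched.

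**What to change.** 1. At follow-up 1, ask about service use and screenings since the baseline assessment, prompted with its date. Keep 6 months at follow-up 2.
2. Report every period as a rate per month, so that baseline and follow-up can be compared.
3. Reconcile the Table 2 headings with the fixed 9 and 15 months in Participant recruitment, so that one timing rule applies to both arms.

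The change is one reworded question stem and one clarified heading, to be made before the first follow-up 1 assessment. The price is somewhat less accurate recall over 9 months and recall lengths of 6, 9 and 6 months. Monthly rates put these on one scale but do not remove differences in recall error, so change from baseline should be read with that in mind. If the longer recall is unacceptable, name another source for months 0–3, such as service records.

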### The intervention

#### Overview of the intervention

We will recruit and train volunteers to act as Health Champions. These Health Champions will support individual service users to set and work towards their own individually decided physical health goals. They will meet face-to-face once a week for up to 9 months at a location decided by the participant and in line with their goals or remotely depending on the guidance on social distancing at the time. If the participant reaches their goals within 9 months, they can choose to end their involvement. The Health Champions will be supported by a Volunteer Coordinator who will be based in the SLaM Volunteer team and will be recruited specifically for this role.

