### Aim 2: Implementation effectiveness of the intervention

#### Primary outcome

Our primary outcome is acceptability of the intervention measured using the Acceptability of Intervention Measure [17].

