#### Feasibility outcomes

Feasibility of the intervention measured using the Feasibility of Intervention Measure [17] and qualitative interviews with participants and Health Champions.Appropriateness of the intervention to both participants and Health Champions measured using the Intervention Appropriateness Measure [17] and qualitative interviews with participants and Health Champions.Fidelity to the intervention which we will measure using a content analysis of Health Champions and participants journals to assess fidelity of the delivery of the intervention and fidelity of receipt of the intervention, supervision records and the number and percentage of meetings between each Health Champion and participant.Barriers and facilitators and unintended consequences will be measured using qualitative interviews with a subset of 30% participants and Health Champions chosen at random after the intervention recording whether the intervention was delivered face to face or remotely plus details from the journals and supervision records. We will also interview all participants who drop out of the intervention to understand their reasons for this.Adoption of the intervention will be measured by the number and percentage of participants that start the intervention, how many sessions they have and how long (in months) they stay in the intervention.Adoption and sustainability will also be assessed using interviews with SLaM managers and commissioners.

### Data analysis for aims 1 and 2

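### The primary implementation outcome, acceptability, is scored by participants once, at follow-up 1, and is not attached to the interview planned for people who drop out of the intervention, so the score may over-represent those who stayed

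*Protocol article*

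**What the plan says.** The Aim 2 primary outcome section states: "Our primary outcome is acceptability of the intervention measured using the Acceptability of Intervention Measure". It names no rater and no time point. Those come only from Table 2, which lists the "Acceptability of intervention measure" in a participant row that reads "Acceptability 1. Acceptability of intervention measure 2. Interview" and carries a single mark, in the follow-up 1 column. Health Champions have a matching row, also marked once at follow-up 1.

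The timing of follow-up 1 is given in two ways. The Table 2 column is headed "Follow-up assessment 1 (at end of intervention or after 9 months"). Participant recruitment says: "Both groups will be asked to complete follow-up assessments at 9 months and 15 months after baseline". The Aim 1 primary outcome section agrees with the latter, treating the end of the intervention and nine months after baseline as the same moment. Overview of the intervention, however, allows an earlier end: "If the participant reaches their goals within 9 months, they can choose to end their involvement".

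For people who leave the intervention, both Feasibility outcomes sections say: "We will also interview all participants who drop out of the intervention to understand their reasons for this". No questionnaire is mentioned for that interview, and neither its timing nor a row for it appears in Table 2.

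**The concern.** Someone who finds the intervention unacceptable is a likely candidate to stop meeting the Champion, and plausibly also to be harder to reach later. If the only acceptability score is taken at 9 months, the people with the least favourable views may be under-represented in the primary implementation outcome. The one contact designed for them collects reasons but no score.

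Analysis cannot easily make up for this. The likelihood-based mixed models under Quantitative data use repeated time points and assume that data are missing at random. Participants' acceptability has no baseline value and no second measurement, so a missing score has no earlier score from the same person to draw on, and non-response may depend on acceptability itself. At stake is whether the acceptability figure taken forward to a definitive trial describes everyone offered a Champion or mainly those who continued.

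**Working it through.** The point rests mainly on setting the provisions side by side.

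1. **Are early leavers still due the measure?** Yes. Under the Table 2 heading, follow-up 1 can fall at the end of the intervention, which can cover an early ending. Under Participant recruitment, both groups are followed at 9 and 15 months, with no exception for people who stop the intervention.

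2. **When would they be scored?** This depends on which wording is followed. Take a person who stops at month 2. Under the 9-month wording the measure comes 9 − 2 = 7 months later, if the person is still reachable. Under the Table 2 heading it could come at month 2.

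3. **Is there another chance to obtain a score?** No. There is one mark in Table 2, no measure at the dropout interview, and no acceptability score at follow-up 2.

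4. **How many might have no score?** The documents do not say. The nearest figure is under Sample size: 60 recruited per arm to leave 50, a loss of 10/60 = 16.7%. No dropout rate is stated, but 100/(1 − 1/6) = 120 reproduces the recruitment target. These are losses from the study, for any reason and in either arm. They are not people who stopped the intervention because they disliked it.

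5. **Illustration.** Assume that 10 of 60 intervention participants have no score and that a proportion p of the 50 scored rate the intervention acceptable. With no assumption about the unscored, the proportion among all 60 lies between 50p/60 and (50p + 10)/60:

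| Observed p among 50 | Lower bound for 60 | Upper bound for 60 |
|---|---|---|
| 60% | 30/60 = 50.0% | 40/60 = 66.7% |
| 80% | 40/60 = 66.7% | 50/60 = 83.3% |
| 90% | 45/60 = 75.0% | 55/60 = 91.7% |

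On a mean score, if the unscored would have rated d points lower on average, the observed mean is too high by (10/60) × d: 0.17 for d = 1, 0.25 for d = 1.5 and 0.33 for d = 2. The values of p and d, the cut for acceptable, and the use of 10 of 60 are assumptions. The documents give neither the scale of the measure nor a threshold.

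**The case against.** The strongest reply is that nobody is excluded. Stopping the intervention is not leaving the study, and early leavers are due follow-up 1 on either wording. What remains is attrition, which touches every outcome. The plan also collects reasons from all dropouts and reports how many start, how many sessions they have and how long they stay, so a favourable score would be read beside retention data. Most of this stands. A reader might infer from the single time point that acceptability is simply not measured in people who leave early; the documents do not support that. What survives is narrower: for those not reached at follow-up 1 no acceptability score exists, although the plan intends to speak to those who drop out of the intervention.

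A reader might also infer that controls are asked to rate an intervention they never received, because the participant block of Table 2 is not split by arm. That is only a literal reading. No section says that controls complete the measure, and the same block holds rows, such as the interview on experience of the intervention, that make sense only for recipients. A condensed article may leave such a footnote to the full protocol.

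Finally, it is tempting to treat acceptability as the score that decides progression. No threshold on it is stated, and the quantity named to guide a larger trial is the change in EQ-5D-5L.

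**Conclusion.** The point holds as a modest one. The primary implementation outcome has a single participant time point, its timing is described inconsistently, and the contact planned for people who drop out of the intervention does not include the measure. The score is liable to over-represent those who stayed.

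The size of any bias cannot be derived from the documents, and the figures above only show what a loss of the planned order could conceal. An upward bias is plausible but not shown. It assumes that the people left unscored are less favourable than the rest, and some early endings occur because goals were reached, where ratings may well be good. This is a cheap improvement to data collection. It does not show that the outcome is invalid.

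**What to change.** - Have intervention participants who stop early complete the acceptability, appropriateness and feasibility measures at the dropout interview already planned, and state when that interview takes place.
- Reconcile the timing of follow-up 1 between the Table 2 heading, Participant recruitment and the Aim 1 primary outcome section, so that it is clear when someone who ends before 9 months, including by reaching their goals, is scored.
- Report the measures for all intervention participants with a score, and separately for completers and early leavers, stating how many in the arm have none. People who never start or who decline contact will still be missing, and the count makes that visible.
- As a minor clarification, mark these Table 2 rows as intervention arm only.

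The cost is three short questionnaires added to an existing interview, which becomes slightly longer, and small edits to Table 2 and the text.
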